## Methods

### Study Design

This study is a double-blind, randomized, placebo-controlled crossover trial. The crossover design allows each participant to serve as their own control across 3 intervention phases. Each participant will complete a 12-week protocol comprising a 1-week run-in period followed by 3 intervention phases, each separated by a 4-week washout period. A total of 6 study visits, comprising 3 preintervention and 3 postintervention assessments, will capture baseline and postintervention data. During the run-in and washout periods, participants will maintain their habitual diet and physical activity. The study will be conducted at a government primary care facility situated in an urban area. Recruitment will be facilitated through clinic listings and physician referrals. Written informed consent will be obtained after participants receive detailed verbal and written explanations of the study procedures, risks, and rights. The study timeline is summarized in Figure 1.

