### Participants

This study aims to recruit a cohort of clinically stable patients representative of Malaysians with early-phase T2DM. Eligible participants will be males aged 30 to 59 years, with a BMI of 23.0 to 29.9 kg/m², classified as overweight [21]. Participants must have a clinical diagnosis of T2DM for 1 to 10 years, with baseline glycated hemoglobin (HbA_1c_) below 10%, and be managed with oral antidiabetic medications only. Individuals with stable, nonsevere chronic conditions, such as hypertension or dyslipidemia, will be included if they have maintained a consistent oral treatment regimen for at least 6 months before enrollment. All participants must have previously received dietary counseling for diabetes and agree to maintain their habitual diabetes-friendly diet and regular physical activity throughout the study. They must abstain from alcohol consumption during the intervention period and be literate in either English or Bahasa Malaysia to ensure full understanding of the study procedures and informed consent materials.

Exclusion criteria focus on lifestyle or dietary patterns that deviate from typical Malaysian practices or that could substantially alter the gut microbiota. Individuals will be excluded if they currently smoke or consume alcohol, have experienced more than 5% body weight change within the past 3 months, or have acute illness or major comorbidities, such as cardiovascular, psychological, neurological, renal, or endocrine disorders other than T2DM. Those with known intolerance or allergy to the test products, adherence to special diets (eg, vegetarian, ketogenic, or intermittent fasting), or use of medications or supplements (eg, probiotics) that may affect intestinal function or microbiota composition will also be excluded. Participation in another clinical trial within the past 3 months will preclude eligibility. Participants may withdraw voluntarily or be withdrawn for safety reasons, protocol deviation, or the need for antibiotic therapy. Diabetes management will continue as per clinical practice. Adverse events will be monitored and managed by the study physician following institutional protocols.

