**Questionnaire**								
	Sociodemographic and medical history	✓						
	Medication record	✓	✓		✓		✓	
	Dietary record	✓	✓	✓	✓	✓	✓	✓
	Physical activity record	✓	✓	✓	✓	✓	✓	✓
	Test product compliance record			✓		✓		✓
	Adverse effect reports			✓		✓		✓

Anthropometric measurements will be obtained using standardized procedures. Body weight will be measured using a calibrated digital scale with participants wearing light clothing, while height will be measured using a stadiometer, ensuring an upright posture and proper head alignment. The average of 2 readings will be recorded for both weight and height, and BMI will be calculated as weight in kilograms divided by height in meters squared (kg/m²). Waist circumference will be measured at the midpoint between the lowest rib and the iliac crest using a nonstretchable measuring tape [25]. Body composition, including body fat and muscle mass, will be assessed using bioelectrical impedance analysis following standard premeasurement guidelines [26]. Blood pressure will be measured twice after a 5-minute rest using an automated sphygmomanometer, and the mean of both readings will be recorded.

For biological specimens, blood samples of approximately 15 mL will be collected from participants at each study visit by trained nurses after a 30-minute rest period. Analyses will include fasting glucose, fasting insulin, glycated hemoglobin (HbA_1c_), lipid profile, and kidney function indicators. Insulin resistance will be estimated using the HOMA-IR, derived from fasting glucose and insulin levels [27]. Samples will be transported and processed according to biosafety and quality control procedures to ensure sample integrity for biochemical analysis and future molecular investigations. Stool samples of approximately 1 g will be collected using standardized fecal collection tubes provided to participants. Preintervention samples will be collected a day before each intervention phase, and postintervention samples will be obtained immediately after the final intervention day. Participants will receive detailed written and verbal instructions to ensure correct collection and handling procedures [28].

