### Statistical Analysis

Clinical data will be presented as mean (SD) unless stated otherwise. Statistical analyses will be performed using SPSS Statistics (version 28.0; IBM Corp) [40]. The normality of continuous variables will be assessed using the Shapiro-Wilk test. Participants’ baseline characteristics will be summarized using descriptive statistics. Differences in glycemic responses across the 3 study arms will be assessed using either 1-way ANOVA or the Kruskal-Wallis test, depending on data distribution. Changes in clinical variables before and after the intervention will be analyzed using repeated-measures ANOVA, with time (before vs after), group (intervention arm), and the time-by-group interaction as factors. Sociodemographic characteristics, dietary intake, and physical activity levels will be considered as covariates where appropriate. A *P* value of <.05 will be considered statistically significant. Analyses will be conducted according to the intention-to-treat principle, with per-protocol analyses performed for participants who complete the study without major deviations. Missing data will be handled using appropriate imputation methods, and any exploratory analyses will be clearly identified and interpreted with caution.

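### The per-protocol set is defined by participant, so one bad phase discards that man's validly measured phases; a phase-level definition and a mixed model would keep them

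*Protocol article*

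**What the plan says.** The Statistical Analysis section sets two populations in one sentence: "Analyses will be conducted according to the intention-to-treat principle", "with per-protocol analyses performed for participants who complete the study without major deviations". The next sentence adds "Missing data will be handled using appropriate imputation methods" and names no method. Changes in clinical variables are to be tested by "repeated-measures ANOVA, with time (before vs after), group (intervention arm), and the time-by-group interaction as factors". Differences between arms in glycemic response are to be tested "using either 1-way ANOVA or the Kruskal-Wallis test, depending on data distribution".

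Other sections describe a design that works by phase:

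- Study Design: "The crossover design allows each participant to serve as their own control across 3 intervention phases". There are six visits, one before and one after each phase, and the phases are separated by 4-week washouts.
- Data Collection, Table 1: the row "Test product compliance record" is ticked at Visits 2, 4 and 6, so compliance is known separately for each phase.
- Participants: "Participants may withdraw voluntarily or be withdrawn for safety reasons, protocol deviation, or the need for antibiotic therapy". An event in one phase can therefore leave later phases unobserved.
- Sample Size: a within-subject repeated-measures ANOVA with three conditions needs 28 men; 33 are recruited to cover dropout or noncompliance.

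**The concern.** In a crossover, each pair of completed phases gives a within-person comparison. A man with a major deviation only in his saccharin phase still supplies a usable comparison of sucralose with placebo. The stated rule takes him out of the per-protocol set altogether, although the data needed to judge each phase separately are collected. The per-protocol analysis loses precision and is confined to men who complied with all three products.

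Intention-to-treat raises a related question. The standard within-subject ANOVA with three conditions needs all three conditions from every participant. A man who misses a phase must then be dropped, which goes against intention-to-treat, or have the phase imputed. A mixed model needs neither.

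**Working it through.** **1. The plan's own figure.** Inputs from Sample Size: f = 0.25, m = 3 conditions, r = 0.5, α = 0.05, power 80%. The noncentrality is λ = N·m·f²/(1 − r), with degrees of freedom m − 1 = 2 and (N − 1)(m − 1).

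- N = 27: λ = 27 × 3 × 0.0625 / 0.5 = 10.125, power 0.796.
- N = 28: λ = 10.5, power 0.812.
- N = 33: λ = 12.375, power 0.878.

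The smallest N reaching 80% is 28, as stated. Recruiting 33 allows for a loss of 5/33 = 15.2%.

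**2. Retention under the person-level rule.** Let q be the chance of a major deviation or loss in a phase, independent across phases. The article gives no rate, so q is an assumption. Men retained = 33(1 − q)³. Clean phases discarded = 99(1 − q) − 99(1 − q)³.

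| q | Men retained | Clean phases discarded | Power with those retained |
|---|---|---|---|
| 3% | 30.1 | 5.7 | 0.84 |
| 5% | 28.3 | 9.2 | 0.82 |
| 8% | 25.7 | 14.0 | 0.77 |
| 10% | 24.1 | 16.9 | 0.74 |
| 15% | 20.3 | 23.4 | 0.66 |

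The number retained falls below 28 once q exceeds 1 − (28/33)^(1/3) = 5.3%.

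**3. Variance of a sweetener-placebo contrast.** This is the generalised least squares variance with product and phase fixed and participant random, for 33 men, 11 per order in three cyclic orders. The within-person correlation was set at 0, 0.3 and 0.5. The ratio compares the person-level rule with keeping every clean phase.

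- Check by hand at correlation 0, using expected counts: (1 − q)/(1 − q)³ = 1/(1 − q)². This is 1/0.9025 = 1.11 at 5% and 1/0.81 = 1.23 at 10%.
- Averaged over random deviation patterns and the three correlations: about 10-12% larger at 5%, and about 22-25% larger at 10%. Repeat runs move the ends of these ranges by about one percentage point.
- As confidence-interval width: √1.10 to √1.12 is 5-6% wider; √1.22 to √1.25 is 10-12% wider.

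**4. A case matched to the plan's allowance.** Suppose 5 of 33 men each lose exactly one phase, with r = 0.5. For n complete men the contrast variance is 2(1 − r)/n = 1/n.

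- Completers only: 1/28 = 0.0357, power 0.812. Ten clean phases are discarded.
- All 84 + 10 = 94 observed phases in the mixed model: variance 0.0325, so the effective number of complete men is 1/0.0325 = 30.8 and power is about 0.85.
- If the five instead leave the trial, half after phase 1 and half after phase 2: variance 0.0336, effective number 29.8, power about 0.84.

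**The case against.** The strongest reply is that little depends on this. Intention-to-treat is the governing principle and the per-protocol analysis only accompanies it, so the excluded men are not lost to the trial. A participant-level per-protocol set is a common convention. The sample size already budgets for losing whole people: at 5% per phase about 28 men remain, which is the planned number, and power is about 0.82. The 10% scenario needs frequent major deviations in 7-day phases with once-daily dosing. Phase-level exclusion also selects on compliance after randomisation, and a deviation could affect a later phase. The withdrawal rule means that later phases may not exist to be kept. All of this stands; it limits the size of the point but does not make the person-level definition the better one.

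A reader might infer more: that the plan compels whole unseen phases to be filled in for products a man never took. The text does not support that. It names no imputation method, does not say that unstarted phases will be filled, and does not say whether group is a within- or between-subject factor. The 1-way ANOVA and Kruskal-Wallis wording suggests that arms might be treated as separate groups, in which case observed phases could enter without imputation. That reading ignores the pairing and sits badly with the sample-size model, but the text leaves it open. The imputation method is also something an article may leave to the full protocol or SAP.

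A reader might also expect an inflated false-positive rate. Simulation gives about 7-7.5% if missing phases are filled with arm means, but the plan never names that method, so the figure is not a property of this plan.

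**Conclusion.** The per-protocol half holds on the text: the set is fixed by person and by study completion, and one bad phase removes valid ones. The intention-to-treat half holds only conditionally: if the ANOVA is run as the within-subject test of the Sample Size section, a man missing a phase must be imputed or dropped.

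The size depends on deviation rates that the article does not give. At an assumed 5% per phase the loss is modest and the 80% target is still met. At an assumed 10%, about 24 men remain and power in that set is about 0.74. Both assume independent deviations and an equal correlation between phases. No stated figure is wrong. This is a cheap improvement to the analysis, not an error in the plan.

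**What to change.** 1. For intention-to-treat, replace repeated-measures ANOVA plus unspecified imputation with a linear mixed model fitted to all observed phases, with product and phase as fixed effects and participant as a random effect. It is valid under missing at random. Keep imputation as a sensitivity analysis.
2. Define the per-protocol set by participant-phase: exclude only the phase with the major deviation and keep the man's other phases in the same model.
3. Report the number of participants behind each contrast, and state the assumption that a deviation does not carry over into later phases.

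The cost is analysis wording. SPSS, already named in the article, fits such models; no new data are needed, and no participant had been enrolled as of December 2025. The drawbacks are that the number of participants differs between contrasts and that the carry-over assumption in step 3 is needed.

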## Results

Recruitment for this trial is scheduled to commence in January 2026 and is expected to conclude by September 2026. Data collection and analysis will be conducted sequentially after each intervention phase, with overall completion anticipated by March 2027. As of December 2025, no participants have been enrolled.

## Discussion

This protocol outlines a trial designed to examine the short-term effects of NNSs, specifically sucralose and saccharin, on glycemic control and gut microbiota composition among patients with T2DM. Glycemic control continues to be a central focus in diabetes management, and growing evidence suggests that the gut microbiota plays a significant role in regulating glucose metabolism [41]. Therefore, investigating these 2 domains concurrently in individuals with T2DM is both timely and clinically relevant. This study addresses a critical knowledge gap, as most prior research has focused on healthy populations, leaving limited evidence regarding metabolic and microbial responses in people with T2DM [2-4,7-13,42]. To date, only 1 study conducted in 2003 has examined the impact of sucralose consumption on glycemic control among individuals with T2DM, reporting no significant effects [43]. Among healthy participants, findings on both glycemic regulation and gut microbiota modulation following sucralose or saccharin intake have been inconsistent. Some studies have reported decreased insulin sensitivity after sucralose or saccharin consumption [2-4,10-13], whereas others have found no meaningful changes in glucose metabolism [7-9,42]. Similarly, evidence regarding gut microbiota alterations remains inconclusive, with several investigations observing significant shifts in microbial composition [2-4], while others have reported no detectable differences [7,9]. These discrepancies likely arise from variations in study design, intervention duration, dosage, sweetener formulation, and participant characteristics. Differences in demographic, dietary, and lifestyle factors also contribute to heterogeneity and make comparisons between studies challenging.

This trial aims to overcome these inconsistencies through a tightly controlled crossover design, enabling each participant to serve as their own control and thereby minimizing interindividual variability. A 1-week intervention period was selected to assess short-term effects while maintaining participant compliance and feasibility, followed by a 4-week washout period to avoid carryover effects. The selected NNS dosages represent the upper acceptable daily intake recommended in medical nutrition therapy guidelines, ensuring both safety and sufficient exposure to detect measurable outcomes [22]. Capsules will contain pure sucralose or saccharin to isolate the effects of the sweeteners themselves, excluding confounding components from commercial formulations. Recruitment through government health care facilities allows for a clinically characterized sample reflective of the local T2DM population. Restricting participation to males within a defined age and BMI range enhances phenotype consistency, while inclusion criteria based on disease duration and treatment regimen further standardize metabolic profiles. Gut microbiota profiling using 16S rRNA sequencing targeting the V3-V4 region will facilitate comparison with established microbiome literature [44].

Several limitations warrant consideration. The relatively short intervention period and modest sample size may not capture longer-term or subtle metabolic and microbial changes. Although participants will be encouraged to maintain their usual diet and physical activity, residual variability in lifestyle behaviors could influence outcomes. These confounders will be monitored using validated dietary and physical activity recall tools to aid interpretation. Furthermore, as limited baseline microbiome data are available for Malaysian individuals with T2DM, observed microbial shifts should be interpreted within the context of population-specific dietary and genetic factors. Nonetheless, the comprehensive baseline characterization and rigorous design of this study are expected to strengthen internal validity and provide a valuable foundation for future investigations.

In conclusion, this trial will generate novel evidence on short-term metabolic and microbial responses to NNSs in individuals with T2DM. Findings may help refine dietary recommendations and guide policy decisions regarding NNS consumption in Asian populations with T2DM. Beyond clinical implications, the results are expected to inform public and industry perspectives on NNS safety and contribute to the broader understanding of gut microbiome-metabolism interactions, supporting the design of future large-scale and longer-term clinical trials.

## Appendix

Multimedia Appendix 1 Peer review report by The Fundamental Research Grant Scheme (FRGS), Ministry of Higher Education Malaysia.

## Abbreviations

HOMA-IR: homeostatic model assessment for insulin resistance
NNS: nonnutritive sweetener
T2DM: type 2 diabetes mellitus
